#### Cost-effectiveness analysis

A ‘within-trial’ economic analysis will be conducted alongside the RCT to estimate the incremental cost-effectiveness of the SupportBack 2 interventions compared with usual care. The base case perspective will be that of the NHS, but other resources relevant to LBP will be collected to enable additional analysis from a societal perspective.

The main outcome measure in the economic evaluation will be the quality-adjusted life year (QALY), obtained from the EQ-5D-5L instrument using the published UK value set. In addition, a cost-effectiveness analysis will be carried out using the study primary outcome measure, that is, the cost per point change in back-related physical function measured using the RMDQ will be estimated. Both costs and effects will be estimated using multiple regression, to allow for potential confounders, such as baseline scores for EQ-5D-5L and RMDQ. Standard practice will be followed to calculate incremental cost-effectiveness ratios (ICERs), and present ICER(s) where any one option has both higher costs and increased effects compared with another. ICERs will show incremental cost per QALY or incremental cost per point improvement in RMDQ. Bootstrapping will be used to calculate cost-effectiveness acceptability curves. These will illustrate the effect of uncertainty on study results. Major assumptions made in the analysis will be tested by means of sensitivity analysis. In particular, assumptions made during the costing of the intervention such as the number of individuals who will be using the website will be explored. Similar methods to the main clinical analysis will be used to handle missing data, that is, analysis of patterns of missing data with multiple imputation methods employed if deemed appropriate. The proposed health economics analysis will be detailed in a health economics analysis plan (HEAP) which will be completed before analysis commences. The HEAP will be circulated for comment prior to the health economics analysis. Any digressions from the HEAP will be documented and justified in the final health economics report.

### Process evaluation

A process evaluation will be carried out following Medical Research Council guidelines on process evaluations of complex interventions.^38^ In order to provide a detailed understanding of the SupportBack intervention three aspects will be examined: Implementation, mechanisms of impact (mediators) and context (moderators). A mixed-methods approach will be used to explore these elements.

#### Implementation

Quantitative data describing trial implementation will be presented including number of practices recruited, patient eligibility (including reasons for declined participation where possible, and analysis of screen failures) and recruitment rates. The number of withdrawals from the trial per arm will be presented, along with numbers/percentages of drop-outs from the intervention who do not respond to follow up. Use of the internet intervention will be described by presenting automated data collected on number of logins and modules accessed for both the internet intervention and the intervention plus telephone physiotherapist support arm. With regard to the internet intervention plus telephone physiotherapist support arm, the number of support calls successfully made (and attempts contact the patient), along with the mean number per participant in this arm will be described.

Qualitative interviews will be conducted with up to 45 trial participants following the 3, 6 and 12 months follow-up points. Different participants will be interviewed at each time point, enabling us to explore how time since accessing the tailored weekly component of the intervention effects how suggestions are used and implemented in daily life. Interviews will also be conducted with the trial physiotherapists. Participants will be purposively sampled to ensure diversity in terms of age, sex and symptom severity (physical function, pain intensity and duration). Participants will also be sampled based on high and low usage of the internet intervention and high and low engagement with the telephone physiotherapist support. For participants, questions will focus on their experience of using the intervention, including telephone physiotherapist support and usual care. Interviews with the trial support physiotherapists will be designed to explore their experience of delivering the intervention, with a particular focus on barriers and facilitators, and determinants of successful exchanges.

#### Mechanisms of impact

A logic model of proposed mechanisms affecting LBP-related physical disability and pain outcomes for the SupportBack intervention has been developed (see ref.^14^). This model will be used as the basis of both quantitative and qualitative exploration of mechanisms. Quantitative analyses will focus on psychological and behavioural mechanisms influencing outcome following use of the interventions including expectancy, self-efficacy, PA, self-reported goal setting across the intervention and objective measures of intervention use (sessions completed, use of additional modules, for example, mood, sleep etc). In order to explore whether two core mechanisms’ (mediating variables) contribution to outcome is unique to the internet intervention arms, brief single items capturing SE and PA are being measured in all three arms (including usual care). SE and PA are being measured at baseline and in the outcome questionnaire sets at 6 weeks, 3, 6 and 12 months. Mediation analysis will be used to explore relationships between mediating variables and LBP-related physical function and pain intensity across the 12-month follow-up period. We will also explore the potential of multilevel modelling to examine mediating variables association with the outcome over time.^39^ Appropriate checks of the assumptions of causal modelling, such as exchangeability (no confounding), consistency, effect modification and temporality will also be carried out.^40 41^

Questions will be included in the qualitative interviews focusing on participants’ perceptions of how use of the SupportBack intervention and/or telephone support affected their LBP. This will enable the inductive exploration of participants’ views and triangulation of qualitatively derived theory on mechanism with our quantitative analysis. Similar questions will also be explored in the usual care arm, focusing on how elements of their usual care may have led to improvements in their LBP.

#### Context

The relationship between elements of participants’ context (moderators) and the effect of the interventions across the 12 months follow-up period will be explored. This will include variables such as LBP severity and duration at baseline, age, educational level and occupation status. Following the analysis of mechanisms, correlations and multiple regression (linear and logistic) will be used to explore relationships between moderating variables and LBP-related physical function and pain intensity. Qualitatively, the above aspects of participants’ context, including their own descriptions of their LBP history, will feed into analysis when exploring themes regarding participants use of the intervention and their perceptions of benefit.^42^

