### Sample size

The reported minimally clinical important difference (MCID) between groups for the RMDQ varies. A between group MCID of 2 or 3 points is commonly reported.^23 35 36^ However, it has been suggested that a difference of 1.5 may still be important, particularly in the context of low intensity interventions.^23^ Whether delivered as a stand-alone intervention or coupled with brief telephone support, SupportBack is a low intensity intervention with the potential to be rapidly scalable. Consequently, we considered a between group change of at least 1.5 to be a meaningful difference in this context. For our repeated measures primary outcome, a difference of 1.5 points on the RMDQ over the follow-up period of 12 months, assuming an SD of 5 in line with the feasibility study,^23^ gives an effect size of 0.30. Alpha will be set to 0.025 to allow both interventions to be independently compared with the usual care alone arm. Using four repeated measures (6 weeks, 3, 6 and 12 months), and assuming a correlation between repeated measures of 0.7% and 90% power, requires 215 participants per arm. Allowing for 20% lost to follow-up, this gives a total sample size of 806.

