### Statistical methods

Quantitative analysis will begin following cleaning and inspection of the data. Descriptive analysis will be conducted to determine outliers and distributions of the data. Where necessary, if data are not normally distributed, transformations will be applied or another appropriate distribution used. The primary analysis for the RMDQ score will be performed using a multilevel mixed model framework with observations at 6 weeks, 3, 6 and 12 months (level 1) nested within participants (level 2). Results will be reported adjusting for baseline severity in function, stratification factors and any prespecified confounders. The model will use all the observed data and makes the assumption that missing RMDQ scores are missing at random given the observed data.

As there may not be a constant treatment effect over time, a treatment/time interaction will be modelled and included if significant (at the 5% level), with time treated as a random effect. An unstructured covariance matrix will be used.

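### The moderator analysis aims at effect modification, but the method it names measures association between the moderators and the outcomes

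*Protocol article*

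**What the plan says.** In the protocol article, Process evaluation, Context, the aim comes first: "The relationship between elements of participants’ context (moderators) and the effect of the interventions across the 12 months follow-up period will be explored". The candidate variables follow: "This will include variables such as LBP severity and duration at baseline, age, educational level and occupation status". The method is then that "correlations and multiple regression (linear and logistic) will be used to explore relationships between moderating variables and LBP-related physical function and pain intensity".

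The paragraph mentions no randomised arm, between-arm contrast or interaction in connection with that method. Elsewhere, Statistical methods names one interaction, treatment by time, in the primary model. Mechanisms of impact mentions effect modification, but only among the checks for the mediation analysis: "Appropriate checks of the assumptions of causal modelling, such as exchangeability (no confounding), consistency, effect modification and temporality will also be carried out".

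**The concern.** The aim and the method concern different quantities. A moderator of the intervention effect is a variable across whose levels the difference between arms changes. A variable related to RMDQ or pain intensity at follow-up is a prognostic factor, and it may be one with exactly the same treatment effect at every level. Baseline severity is the obvious example. It is on the list of candidate moderators, and Statistical methods already adjusts the primary model for baseline function, so a strong association with later RMDQ is to be expected whether or not it modifies anything.

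Read literally, the analysis could present prognostic variables as moderators of SupportBack and overlook a variable that truly changes the benefit. The article foresees wide implementation if the intervention works, so an incorrect account of who benefits could be carried into targeting.

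**Working it through.** **1. Aim against method.** The aim is the relation of context variables to "the effect of the interventions across the 12 months follow-up period will be explored". In a linear model with arm T (intervention or usual care) and moderator M,

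E(Y) = b0 + b1·M + b2·T + b3·M·T,

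that aim is the coefficient b3. A correlation of M with Y, or a regression of Y on M with or without T, estimates the association of M with outcome averaged over the arms. It carries no information on b3.

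**2. The plan's own figures.** From Sample size: difference 1.5, "assuming an SD of 5 in line with the feasibility study", four follow-ups, correlation 0.7 (printed with a stray percent sign), 90% power, and "Alpha will be set to 0.025 to allow both interventions to be independently compared with the usual care alone arm".
- SD of the mean of four follow-ups: 5 × √[(1 + 3 × 0.7)/4] = 5 × √0.775 = 4.40.
- n per arm = 2 × (2.241 + 1.282)² × 4.40² / 1.5² ≈ 214, with alpha 0.025 two-sided. The article states 215.
- Total: 3 × 215 / 0.8 = 806.25. The article states 806.

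The sample size reproduces. It serves the main comparison; the article gives no figure for the moderator analysis.

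**3. A purely prognostic variable, pooled over arms.** Analysed participants: 3 × 215 = 645. Assumed correlation with outcome r = 0.2 (not from the article), with no effect modification, tested at two-sided 5%.
- Fisher z: arctanh(0.2) × √(645 − 3) = 0.2027 × 25.34 = 5.14.
- Probability of significance: P(Z > 1.96 − 5.14) = 99.9%.

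**4. Simulation.** 2,000 runs, one intervention arm against usual care, 215 per arm, SD 4.40, average treatment effect 1.5 points, two-sided 5%. The 50/50 binary moderator and the 3-point effects are assumptions. The table gives the share of runs with a significant result.

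| Truth | Y on M | Y on M and arm | M-by-arm term |
|---|---|---|---|
| Prognostic 3 points, no moderation | 100% | 100% | 5.4% |
| Moderation 3 points, no average prognostic effect | 4.3% | 4.0% | 93.6% |
| Neither | 4.9% | 4.9% | 4.3% |

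Regression without the product term responds to prognosis and stays at chance level when there is only moderation. Adding arm as a covariate does not change this.

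**5. Precision of the interaction.** For one intervention against usual care, with 215 per arm and a moderator present in share p:

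SE = 4.40 × √[(2/215) × (1/p + 1/(1 − p))].
- p = 0.5: SE = 0.85, against 0.42 for the main comparison.
- Power for a 1.5-point interaction at alpha 0.025: 1.5/0.849 − 2.241 = −0.47, so 32%. At alpha 0.05 it is 42%.
- p = 0.2 to 0.3: 20% to 27% at alpha 0.025, and 29% to 37% at 0.05.
- Interaction detectable with 90% power, p = 0.5: 2.99 points at alpha 0.025, 2.75 at 0.05.
- n per arm for 90% power on 1.5 points at alpha 0.025, p = 0.5: 4 × 214 = 856.

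**The case against.** The best defence is that multiple regression is a broad term. A regression with a product term is a standard test of moderation, and the same paragraph calls the variables moderators and names the intervention effect as the target. Mechanisms of impact describes the mediation analysis in nearly the same shorthand, also without mentioning arm, so the phrase may never have been meant as a model specification. The article leaves full analytical detail to a statistical analysis plan that is not at hand.

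Part of this stands. A reader might infer that the planned analysis cannot answer the moderation question in any form. The text does not support that, because it neither includes nor excludes a product term. A reader might also infer that the repeated-measures structure is abandoned. That is not supported either: the question is set over the whole 12 months, and nothing restricts the regression to one time point. Finally, the 99.9% might be taken as the false-positive rate for moderation in this trial. It rests on an assumed correlation, and the article states no rule under which a significant association would be declared moderation.

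The mismatch itself remains. The article did not leave the method open; it named one, and described it as relating moderators to outcomes. Correlations pooled over arms cannot hold an interaction term, and no other section supplies one.

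**Conclusion.** The point holds as a mismatch between a stated aim and a stated method. The correlations, and any regression without a moderator-by-arm term, identify prognostic factors and do not test effect modification. The 99.9% and the simulation illustrate how far the two can diverge; they assume r = 0.2, a 50/50 moderator and 3-point effects, none of which the article gives, and they do not predict what this trial will report.

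The severity is modest. The analysis is an exploratory part of the process evaluation, and the primary comparison, its alpha and the sample size are untouched. If the statistical analysis plan already specifies moderator-by-arm terms, all that remains is to align the wording.

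**What to change.** Replace the method sentence in Context with one along these lines:

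*For each prespecified moderator, moderator-by-arm interaction terms (each intervention versus usual care) will be added to the primary mixed model for RMDQ and to the corresponding model for pain intensity. Continuous moderators will be kept continuous. Interaction estimates with confidence intervals will be reported as exploratory.*

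Associations between these variables and outcome may still be reported if they are labelled as prognostic.

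The cost is the wording and a few further model fits, with no new data. The drawback is low precision: the interaction standard error is about twice that of the main comparison for an evenly split moderator, and larger for an uneven one. A non-significant interaction should therefore not be read as evidence of a uniform effect.

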#### Qualitative analysis

Interview data collected regarding implementation, mechanisms and context will be transcribed verbatim, coded and analysed using an inductive thematic analytic approach.^43 44^ This will ensure participants’ qualitative data are not constrained by the direction of a particular theoretical model, and enable novel insights from qualitative work to be added into the theory-driven logic model. A key aspect of the qualitative analysis will entail exploring differences in accounts at different time points. This will enable us explore how time since the tailored weekly sessions impacts on the process of self-management.

### Data monitoring and confidentiality

The SupportBack 2 trial has a data monitoring and ethics committee (DMEC) composed of a statistician (chair) and two academic clinicians (Professor in Primary Care Research and Professor of Physiotherapy respectively). The DMEC reports to the TSC and is fully independent from the trial Sponsor with no competing interests. Interim descriptive analyses are prepared for the DMEC. The DMEC charter can be obtained from the research team on request.

All serious adverse events (SAEs) are reported to the lead clinical trial unit. The assessment of seriousness will be made by the participants GP or delegate. Assessment of causality will be made by the GP or delegate, and related or unrelated status will be determined. As the SupportBack intervention provides reassurance and encourages gentle activity within the participants’ own limits, there are no ‘expected’ SAEs documented.

All patient data are being kept in strict confidence and managed in accordance with the Data Protection Act 2018 and General Data Protection Regulation (2018) legislation. The University of Southampton policy on archiving will be followed; the data will be stored for 10 years following the end of the study, after which time it will be disposed of securely. Following completion of the trial, a cleaned anonymised data set will be shared on request.

### Patient and public involvement

Patient representatives have been involved with the SupportBack trials from the outset. The idea for the trials and their subsequent design was informed by the local branch of the national charity BackCare. From this group, LL joined the research team and contributed to funding applications for both feasibility and main trials. SupportBack 2 has a panel of three patient and public involvement (PPI) representatives who are part of the trial management group, advising on patient facing materials and contributing to discussions of trial related issues as they arise. PPI will pay a key role in dissemination of trial findings and interpretation of qualitative data.

### Ethics and dissemination

The SupportBack 2 trial has received full ethical approval form a local review board (REC Ref: 18/SC/0388). All potentially eligible patients receive a patient information sheet. This information emphasises that participation in the trial is voluntary and that the participant may withdraw from the trial at any time for any reason. The participants are given the opportunity to ask any questions that may arise by speaking with the trial team and time to consider the information fully prior to agreeing to participate.

The findings of this trial will be published in peer-reviewed journals and presented at international conferences. We will develop press releases in order to disseminate the findings to the general public, and work closely with our PPI collaborators to ensure dissemination to patient and other special interest groups. A summary of the findings will be sent to all included general practices and those patients that request this information. If the intervention is shown to be effective, we will work with developers to rapidly develop a version for widescale dissemination and implementation.
